## Abstract

**Background:**

Delirium is very common in critically ill patients admitted to the intensive care unit (ICU) and results in negative long-term outcomes. Family members are also at risk of long-term complications, including depression and anxiety. Family members are frequently at the bedside and want to be engaged; they know the patient best and may notice subtle changes prior to the care team. By engaging family members in delirium care, we may be able to improve both patient and family outcomes by identifying delirium sooner and capacitating family members in care.

**Methods:**

The primary aim of this study is to determine the effect of family-administered delirium prevention, detection, and management in critically ill patients on family member symptoms of depression and anxiety, compared to usual care. One-hundred and ninety-eight patient-family dyads will be recruited from four medical-surgical ICUs in Calgary, Canada. Dyads will be randomized 1:1 to the intervention or control group. The intervention consists of family-partnered delirium prevention, detection, and management, while the control group will receive usual care. Delirium, depression, and anxiety will be measured using validated tools, and participants will be followed for 1- and 3-months post-ICU discharge. All analyses will be intention-to-treat and adjusted for pre-identified covariates. Ethical approval has been granted by the University of Calgary Conjoint Health Research Ethics Board (REB19–1000) and the trial registered. The protocol adheres to the Standard Protocol Items: Recommendations for Interventional Trials (SPIRIT) checklist.

**Discussion:**

Critically ill patients are frequently unable to participate in their own care, and partnering with their family members is particularly important for improving experiences and outcomes of care for both patients and families.

**Trial registration:**

Registered September 23, 2019 on Clinicaltrials.gov NCT04099472.

## Background

Patients admitted to the Intensive Care Unit (ICU) are the sickest in the healthcare system; they have complex medical problems that require urgent treatment with life sustaining technologies [1]. Within this context, one of the largest challenges in the care of critically ill patients is the development of delirium. Delirium (an acute confusional state characterized by fluctuating course, attention deficits, and severe disorganization of behavior [2]) is present in over half of all critically ill patients admitted to ICUs [3–8]. Delirium is associated with negative outcomes in critically ill patients, including longer hospital stays [9], increased risk of long-term cognitive impairment, and death [10–12].

Family members of critically ill patients are also exposed to high levels of stress and are at risk of developing stress-related complications during and after the ICU stay, including sleep disturbances, anxiety, and depression [13]. Witnessing delirium is distressing for families, who watch their loved one's suffering both during and after a hospital stay [14]. Families are essential to the journey of critically ill patients and their participation in care may improve outcomes for both patients and families [15–18]. For example, there was a decrease in symptoms of both anxiety and depression in families who witnessed cardiopulmonary resuscitation [16] and those who received information on what to expect at the end of life [17]. Family involvement in preventing, detecting, and managing delirium has the potential to produce similar positive effects. The *Facilitated Sensemaking* framework [19–21] provides a theoretical basis for patient- and family-oriented studies in the ICU; engaging families in decision making and care provision may enhance their ability to cope with a new and challenging situation. Patients may also benefit from greater inclusion of family members in the ICU. Increased family presence does not increase infection rates [22, 23] or adverse events [23] and may decrease cardiocirculatory complications [24] and reduce patient falls [25]. Delirium is a common and serious complication of critical illness that affects both patients and their family members. ICU patients, family members, providers and decision-makers (ICU stakeholders) recognize the enormity of this issue and stakeholder groups have identified delirium detection and management as a top quality improvement opportunity [26–30].

Despite high prevalence, detrimental effects, and priority as a quality improvement initiative, delirium is often overlooked in the ICU or assumed to be a normal part of a patients’ clinical course [31]. The importance of brain dysfunction in the ICU is increasingly recognized and although formal delirium screening programs have been implemented worldwide, the majority of cases remain undetected [31]. Family members may be able to notice subtle changes in patients’ cognition and behavior before an unfamiliar clinical observer [32]. The prevention and management of delirium is also challenging; the only guideline recommended therapies for delirium are non-pharmacological and there are presently no known effective pharmacotherapies for delirium [33]. Family members may be engaged in these non-pharmacological delirium prevention and management therapies at the bedside through activities such as re-orientation, familiarization, and mobilization [33]. Critically ill patients are frequently unable to participate in their own care; by partnering with their family members (e.g., immediate family, relatives, friends), we may be able to improve experiences and outcomes of care for both patients and families [10, 34, 35]. We hypothesize that structured engagement of family members in the detection of delirium symptoms and prevention and management of delirium using non-pharmacological strategies will decrease the number of symptoms of anxiety and depression in family members of critically ill patients and may decrease the duration and severity of delirium in critically ill patients.

### Study aims

#### Primary aim

To determine the effect of family-administered delirium prevention, detection, and management in critically ill patients on family member symptoms of depression and anxiety, compared to usual care.

#### Secondary aims

To determine the effect of family-administered delirium prevention, detection, and management in critically ill patients on family member symptoms of psychological distress, compared to usual care.To determine the effect of family-administered delirium prevention, detection, and management on the prevalence (ever/never delirium as indicated by an Intensive Care Unit Delirium Screening Checklist [ICDSC] score ≥ 4), duration (total days of an ICDSC score ≥ 4), and severity of delirium (as indicated by the ICDSC score, which ranges from 0 to 8) in critically ill patients, compared to usual care.To determine the effect of family-administered delirium prevention, detection, and management on the diagnosis of the patient with delirium (ICDSC score ≥ 4), compared to usual care.To determine the effect of family-administered delirium prevention, detection, and management on family member knowledge of delirium in critically ill patients, compared to usual care.To determine the effect of family-administered delirium prevention, detection, and management on the burden of delirium (e.g., feelings of helplessness) experienced by family members of critically ill patients, compared to usual care.

### Patient involvement

Inclusiveness, support, mutual respect, and co-building are the core principles that will guide this work [36]. Patient and family member (herein referred to as patient advisors) involvement in the current project began during five meetings held between September 10, 2018 and September 5, 2019; they participated in priority setting initiatives and group discussions alongside other stakeholders (e.g., researchers, clinicians, decision makers). The research questions, protocol, and this paper were jointly developed with patient advisors ([name]) on our team. The patient advisors for this project have worked with our team consenting and recruiting participants for projects in the ICU and will continue to do so for this study. The intervention and questionnaire packages were piloted with patient advisors to determine appropriateness of language and the time commitment required for completion. Patient advisors will be included as authors on resulting publications (including the current paper, [name]) and be directly involved in dissemination through presentation of results to scientific and lay audiences. Our multidisciplinary team of patient advisors, researchers, clinicians, and knowledge users have demonstrated a track record of research success in co-leading national peer-reviewed grants (including the funding for the proposed study) and publishing with patient advisors [26, 37–39]. All patient advisors are compensated for their time.

## Methods

### Study design

We will conduct a multicenter, non-inferiority randomized controlled trial with participants randomly assigned to family-partnered delirium prevention, detection, and management or control (standard patient care). Patients and family members will be recruited from four medical-surgical ICUs located in four hospitals (Foothills Medical Centre [FMC], Peter Lougheed Centre [PLC], Rockyview General Hospital [RGH], South Health Campus [SHC] within a publicly funded healthcare system (Alberta, Canada). FMC (28-beds), PLC (18-beds) and RGH (10-beds) are teaching hospitals, while SHC (10-beds) is a non-teaching hospital. All four ICUs are within the same health region, have the same bed structure (single bed, private room), open visitation policies and standard of delirium care. The research team has access to eCritical MetaVision, a population-based, bedside clinical information system which captures in real time demographic, clinical, and outcome data for all ICU patients in Alberta, including routinely collected clinical measures of delirium and sedation [40]. Patient demographics (e.g., birthdate, sex) and clinical characteristics (e.g., admitting SOFA and APACHE-II scores, ICDSC and RASS assessments, sedation, etc.) will be collected.

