### Statistical analysis plan

All data will be analyzed as intention to treat. Descriptive statistics will be used to summarize the patient and family characteristics. For all analyses, we will consider a two-tailed *p*-value < 0.05 to be statistically significant, and will adjust for multiple comparisons (Bonferroni correction) in the primary analysis where appropriate. For the secondary aims, we will not correct for multiple comparisons with statistical procedures, but rather consider them in our interpretation. Subgroup analyses and a priori *covariates* to be considered are: presence of mechanical ventilation, RASS score, delirium subtype, patient frailty status (based on Clinical Frailty Scale scores), patient age, patient sex, caregiver age, caregiver sex, and baseline levels of symptoms of depression, anxiety, and psychological distress. Linear regression models will be used to assess for effect modification and confounding. Missing data will be tabulated for all outcomes. If more than 5% of outcome data is missing, multiple imputation will be employed; for the primary aim, we will also conduct a sensitivity analysis assuming the data is missing not at random.

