#### Sample size calculation

*Primary Outcome:* To find a difference in the mean score on the PHQ-9 or GAD-7 of 3-points (from 13 to 10), with a standard deviation of 5-points, power of 90%, an alpha level of 0.05, and 20% loss to follow-up (based off of previous mortality rates in the study ICUs [local data]), 72 dyads per group are required (*N* = 144). *Secondary Outcomes:* To find a difference in the proportion of delirium events reported in the medical chart (most conservative estimate based on secondary outcomes selected) of 20% (from 10 to 30%) at 90% power, an alpha level of 0.05, and 20% loss to follow up, 99 dyads per group are required (*N* = 198). The primary outcome requires a smaller sample size, and thus the most conservative number based on a secondary outcome is employed here.

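### The Study design section calls the trial non-inferiority, but its hypothesis, two-tailed test and both sample-size calculations are those of a superiority trial, and the article states no margin

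*Protocol article*

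**What the plan says.** The protocol article names its framework once, under Study design: "We will conduct a multicenter, non-inferiority randomized controlled trial", comparing the family-partnered intervention with standard care. Non-inferiority is not mentioned again.

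The other parts of the article that bear on the framework are these:

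- **Hypothesis (end of Background).** Structured family engagement "will decrease the number of symptoms of anxiety and depression in family members of critically ill patients".
- **Primary aim.** The effect "on family member symptoms of depression and anxiety, compared to usual care".
- **Decision rule (Statistical analysis plan).** "we will consider a two-tailed *p*-value < 0.05 to be statistically significant"; the authors also "will adjust for multiple comparisons (Bonferroni correction) in the primary analysis where appropriate". The same section reports differences in proportions and means between groups and says that the significance of those differences will be calculated.
- **Sample size calculation, primary outcome.** "To find a difference in the mean score on the PHQ-9 or GAD-7 of 3-points (from 13 to 10"), with SD 5, 90% power, alpha 0.05 and 20% loss, giving 72 dyads per group.
- **Sample size calculation, secondary outcome.** 10% v 30% for delirium recorded in the chart, with the same power, alpha and loss, giving 99 per group. This sets the trial size of 198.

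**The concern.** Superiority and non-inferiority trials ask different questions and read the same data differently. A superiority trial asks whether the interval for the difference excludes zero. A non-inferiority trial asks whether it excludes a worsening larger than a margin fixed beforehand. The declared framework therefore decides what a non-significant result means: inconclusive in the first case, and possibly a positive finding in the second.

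Here the declared framework is not the one that the hypothesis, test and sample size implement. Being no worse than usual care is also not what the hypothesis claims: the intervention adds education and daily detection to a pamphlet that both groups receive, and it is expected to reduce symptoms. At stake is how the primary result is interpreted if no significant difference is found.

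**Working it through.** **Step 1. Does the plan's own sample size reproduce, and on what basis?**

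Primary outcome (difference 3, SD 5, two-sided 0.05, 90% power):

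n per group = 2 × (1.96 + 1.2816)² × 5² / 3² = 58.4, so 59; the t-test version gives 59.4, so 60.

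With 20% loss: 60 × 1.2 = 72, the stated figure; 59 / 0.8 = 73.75, so 74. A one-sided 0.05 level gives 48 before loss and 58 to 60 after, which does not reproduce 72.

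Secondary outcome (10% v 30%, two-sided 0.05, 90% power):

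- Unpooled variance: (0.10 × 0.90 + 0.30 × 0.70) × (1.96 + 1.2816)² / 0.20² = 78.8; 78.8 / 0.8 = 98.5, so 99.
- Pooled variance: 82; 82 × 1.2 = 98.4, so 99.

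Both stated sizes reproduce as calculations to detect a difference, with no margin as an input.

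**Step 2. Does the arithmetic alone identify the framework?**

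For the primary outcome it does not. A 3-point margin with zero true difference, one-sided 0.025 and 90% power also gives 59 per group. The wording separates the two. A move from 13 to 10 is a fall in symptoms, that is, a benefit to be found, whereas a margin would be a tolerated rise. The 10% v 30% calculation assumes that the groups truly differ and names no margin.

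**Step 3. What could a non-significant result fail to exclude?**

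Evaluable per group: 99 × 0.8 = 79.2, about 79.

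| Case | Calculation | Points |
|---|---|---|
| 95% CI half-width | 1.96 × 5 × √(2/79) | 1.56 |
| Half-width if Bonferroni covers two scales (0.025 each, assumed) | 2.24 × 5 × √(2/79) | 1.78 |
| Upper limit of harm, observed difference zero | 0 + 1.56 | about 1.6 |
| Upper limit of harm, observed worsening just short of significance | 1.56 + 1.56 | about 3.1 |

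The last figure is about as large as the 3-point benefit that the trial is sized to find.

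**Step 4. What would a real non-inferiority design need?**

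The article gives no margin, so a range is assumed (SD 5, true difference 0, one-sided 0.025).

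| Assumed margin (points) | n per group for 90% power, after 20% loss | Power with 79 evaluable per group |
|---|---|---|
| 1 | 658 | 24% |
| 1.5 | 293 | 47% |
| 2 | 165 | 71% |
| 2.5 | 107 | 88% |
| 3 | 74 | 96% |

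The smallest margin with 90% power at 79 per group is 5 × √(2/79) × (1.96 + 1.2816) = 2.6 points.

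**Step 5. Does relabelling as superiority disturb the sample size?**

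No. At 79 evaluable per group, power for 3 points at two-sided 0.05 is 96%. If Bonferroni over two scales is assumed, the requirement is 69 per group, or 69 / 0.8 = 86.25, so 87 after loss. That is below 99.

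**The case against.** The strongest reply is that the label is an isolated slip that governs nothing. It appears once, and no analysis, sample size or interpretation rule uses it. The only stated decision rule is a two-tailed test, under which a non-significant result is simply non-significant. This much stands. A reader might infer that the plan would let a null result be reported as success, but no passage says so. What remains is that the label invites such a reading and nothing in the article rules it out.

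Other parts of the reply also stand:

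- **Margin.** A reader might infer that no margin was ever set. The documents support only that none is stated in this article; a fuller protocol or analysis plan may contain one. That would not remove the conflict, because the hypothesis and the sample-size wording would still describe superiority.
- **Confidence-limit rule and per-protocol analysis.** An article commonly leaves these to a fuller document, so their absence here is not a finding.
- **Neutral elements.** The primary aim fits either framework, and a two-tailed 0.05 level does not by itself exclude non-inferiority, which is often judged from a two-sided 95% interval. The contradiction rests mainly on the hypothesis and the sample-size statements, together with the testing of differences.
- **Precision figures.** The 1.6 points apply only to an observed difference of exactly zero, without Bonferroni correction. The planned covariate adjustment would probably narrow the interval. The figures illustrate precision and do not predict a result.

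**Conclusion.** The contradiction is real and lies within the article. The one sentence that names the framework disagrees with the directional hypothesis, the two-tailed testing of differences and both sample-size calculations, and no other section reconciles them. It is more than clerical, because the declared framework governs how a non-significant primary result is read.

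Its size is in interpretation, not in recruitment. A non-significant result could leave a worsening of about 1.6 points (observed difference zero) to about 3.1 points (observed difference leaning towards harm) unexcluded. These figures rest on SD 5, 20% loss from 99 per group, an unadjusted comparison and a 95% interval; the half-width becomes about 1.8 points if Bonferroni over two scales is assumed. Superiority is the likely intent, judged from the wording of the hypothesis and of the sample-size section and not from the 59 to 60 per group alone.

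**What to change.** In the Study design section, replace non-inferiority with superiority. In the Statistical analysis plan section, add one sentence: a non-significant primary result will be reported with its confidence interval as inconclusive, not as evidence of non-inferiority.

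This changes one word and adds one sentence. The sample size of 198 and the conduct of the trial are unchanged. By the article's own Dissemination section, a modification needs the agreement of the protocol authors and ethics approval. The registry record is not at hand; if it repeats the label, it should be corrected as well. The change should be made before results are known.

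If non-inferiority is truly intended, the correction is larger: pre-specify and justify a margin on each primary scale, state the confidence-limit rule, rewrite the hypothesis to match, and redo the sample size. At the planned size, 90% power is available only for margins of about 2.6 points or more, under the assumptions in the working.

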### Eligibility criteria

Consecutive, eligible (Table 1) patients with at least one family member (defined here as family, relatives, or friends) present in the ICU will be approached by a patient advisor or research assistant to participate (Additional file 1). The patient and family member will be enrolled in the study as a dyad. Participants will be recruited at any point during their ICU admission, and participation will occur to a maximum of 5 days, or until ICU discharge or death. Anticipated study flow is presented in Table 2. If more than one family member is present, the study team will enroll the family member most familiar with the patient or the familiar expected to visit the most (and provide complete data).

**Table 1 Tab1:** Study Inclusion and Exclusion Criteria

	Dyad	
	*Patient*	*Family*
Inclusion Criteria	• Age 18 years of age or above	• Age 18 years of age or above
	• Family member present	• Present
	• Richmond Agitation Sedation Scale score ≥ −3 (eligible for delirium assessment)	
Exclusion Criteria	• Unable to provide informed consent (patient or family member)	• Unable to provide informed consent (patient or family member)
	• Inability to communicate with the research staff (e.g., no hearing impairment and must be fluent in English)	• Inability to communicate with the research staff (e.g., no hearing impairment and must be fluent in English)
	• Anticipated to remain in ICU for less 24 h	• Anticipated to remain in ICU for less 24 h
	• Primary neurological injury (e.g., severe traumatic brain injury, subarachnoid hemorrhage)	
	• Glasgow Coma Scale score < 9

**Table 2 Tab2:** Schedule of enrolment, interventions, and assessments

Activity / assessment	CRF (Yes/No)	Staff Member	-1 Prescreening / consent	0 Baseline / Randomization	T1 Immediately post-randomization	T2 Daily for Remainder of ICU stay	F1 Follow-up 1-month	F2 Follow-up 3-months
Prescreening consent	No	Nurse unaffiliated with study	X					
Screening log	No	Research Assistant	X					
Consent form	No	Research Assistant	X					
Inclusion/Exclusion form	Yes	Research Assistant	X					
Randomization	No	Biostatistician unaffiliated with study		X				
Patient demographics form	Yes	Research Assistant		X				
Family member demographics form	Yes	Research Assistant		X				
Educational video/booklet	No	Research Assistant			X			
Delirium prevention and management	Yes	Research Assistant				X		
Delirium detection (Sour Seven)	Yes	Research Assistant				X		
CIDKQ	Yes	Research Assistant		X		X	X	X
GAD-7	Yes	Research Assistant		X		X	X	X
PHQ-9	Yes	Research Assistant		X		X	X	X
K-10	Yes	Research Assistant		X		X	X	X
DEL-B	Yes	Research Assistant		X		X		
ICDSC	No	Research Assistant		X		X		
RASS	No	Research Assistant		X		X		
CCFNI	Yes	Research Assistant		X				
BCQ	Yes	Research Assistant		X				
CSS	Yes	Research Assistant		X				

*Abbreviations*: *BCQ* Barriers to Care Questionnaire in the ICU, *CIDKQ* Caregiver ICU Delirium Knowledge Questionnaire, *CCFNI* Critical Care Family Needs Inventory, *CSS* Caregiver Coping Strategies, *DEL-B* Delirium Burden, *GAD-7* Generalized Anxiety Disorder 7, *ICU* Intensive Care Unit, *K-10* Kessler Psychological Distress Scale, *PHQ-9* Patient Health Questionnaire 9, *RASS* Richmond Agitation Sedation Scale

